**Summary**

**Introduction:** Maternal health service (MHS) utilization helps to decrease maternal morbidity and mortality. However, the utilization of MHS is very low in Ethiopia and a complex phenomenon affected by several predictors. Its predictors, barriers, and facilitators differ from region to region in Ethiopia, and existing evidence is not sufficient to design effective and efficient strategies. One of the methods to increase the utilization of maternal health care is improving the maternal knowledge about the obstetric danger signs, skills of birth preparedness, and complication readiness practice using health education. However, the effect of health education on these outcomes had not been comprehensively explored and the presently existing studies reported controversial results.

**Objective:** This study aims to improve maternal health service utilization among women of reproductive age in Dale and Wonsho districts of the Sidama region, Ethiopia.

**Methods:** A community-based cross-sectional study will be carried out to assess the utilization and predictors of maternal health care. A phenomenological qualitative study will be conducted to explore perceptions, barriers, and facilitators of maternal health care. A cluster randomized controlled trial will be employed to assess the effect of health education on maternal knowledge about the obstetric danger signs, birth preparedness and complication readiness plan, and maternal health service utilization (MHSU). The minimum required sample size is 1,104 for a cross-sectional study. To explore perceptions, barriers, and facilitators of maternal health care a minimum of 20 in-depth interviews, 3 focus group discussions per group, and 20 key informative interviews will be conducted. The minimum required sample size to assess the effect of health education on outcomes is 1,126. A multi-stage sampling method will be used to select the study participants for a cross-sectional study. A maximum variance sampling method will be used for the qualitative study. A cluster-randomized sampling method will be utilized for the interventional study. Quantitative data will be collected using a validated, pre-tested, and structured questionnaire. Qualitative data will be collected using pre-tested focus group discussions, in-depth interviews, and key informant interviews guides until information saturation is reached. The intervention group will be received 12 rounds of pre-recorded audio-based health education. The utilization of maternal health care will be measured at baseline and 6 months after the intervention. Data will be entered into Epi Data version 3.1 and exported to the SPSS and Stata software for analysis. Descriptive analyses will be carried out to get descriptive measures for the important variables of interest. The generalized estimated equations analysis will be used to assess the potential predictors of MHSU. The coding and analysis of the qualitative data will be done using the thematic content analysis technique by Atlas-Ti software and presented in narratives. For maternal knowledge about the danger signs and practice of birth preparedness and complication readiness, the multilevel linear regression models will be utilized. The intention-to-treat analysis will be used to compare outcomes between groups. Paired and independent t-tests will be used to compare the effect of an intervention. Statistical significance level will be adjusted to account for the effect of multiple comparisons problems using the Bonferroni corrections methods.

**Schedule and budget:** This study will be conducted from October to August 2023; the total cost of the project will be **421,600 ETB (7,026.67 EURO)**.

**Keywords:** Health education, maternal health service, utilization, women of reproductive age, Dale and Wonsho districts, Ethiopia.

**Introduction**

The highest number of maternal mortality, particularly in developing countries is due to low-level utilization of existing maternal health service (MHS) [[1](#_ENREF_1)]. Prior studies in Ethiopia showed that MHSU is very low in general and a significant regional and urban/rural difference exists [[2-7](#_ENREF_2)]. For instance, 43% of pregnant mothers in Ethiopia had 4 or more antenatal care visits whereas 48% gave birth at the health facility, and merely 34% of women received postnatal care within 48 hours after childbirth [[3](#_ENREF_3)] . Likewise, the utilization of maternal and neonatal healthcare services during illness is 6%, 2%, and 3% for pregnant women, postpartum women, and neonates in the Wonago district of Southern Ethiopia, respectively [[4](#_ENREF_4)].

Furthermore, great differences in maternal death happen between the national regional states in Ethiopia. For instance, it is ranged from 74 in the Tigray regional state to 548 mortalities per 100,000 live births in the Afar region [[8](#_ENREF_8)], which briefs the requirement to further study the landscape of utilization patterns of maternal health services at the limited local settings.

The various predictors contributed to the use of the existing MHS and can be categorized as socio-economic and demographic, behavioral, cultural practices and beliefs, organizational, service quality linked predictors, health system functioning, and the lack of transport in rural settings [[2](#_ENREF_2), [4-6](#_ENREF_4), [9-11](#_ENREF_9)]. However, these earlier studies that investigated the utilization of MHS in Ethiopia, focused mainly on individual-level predictors with limited consideration to community-level and contextual predictors. Also, these studies were only quantitative cross-sectional and recommended conducting a further study using a qualitative method to clearly understand the perceptions, barriers, and facilitators of MHSU. These studies also not utilized a multilevel regression model. The predictors, barriers, and facilitators of MHSU differ from region to region in Ethiopia, and utilization of MHS are highly variable and existing evidence is not satisfied to design effective and efficient strategies [[2](#_ENREF_2), [4-6](#_ENREF_4), [9-11](#_ENREF_9)].

The community-level health education intervention (CLHEI) is a fundamental approach to increase maternal knowledge regarding the obstetric danger signs, the practice of birth preparedness as well as complication readiness for emergency complications and MHSU [[12-19](#_ENREF_12)]. However, the effect of a CLHEI on MHSU had not been comprehensively explored and the currently existing literature or evidence is contradicting or reported mixed findings. The several observational and interventional studies conducted in the Sokoto state, Nigeria [[20](#_ENREF_20)], Korogwe district of rural Tanzania [[21](#_ENREF_21)], Kwara state of Nigeria [[22](#_ENREF_22)], Mundri East County, South Sudan [[23](#_ENREF_23)], Alimosho, Lagos State of Nigeria [[24](#_ENREF_24)] and Spain [[25](#_ENREF_25)] showed positive effects.

On the contrary, the interventional studies conducted in Nepal [[26](#_ENREF_26)] and Latin America found that no significant effect of the health education intervention on the perinatal outcomes and use of health facilities service [[27](#_ENREF_27)]. Moreover, a study from community antenatal clinics showed that a general service for initiation of breastfeeding using peer support workers was unsuccessful in enhancing initiation rates of breasting feeding [[28](#_ENREF_28)]. Also, these entire studies do not offer a satisfactory appreciation of the effect of a CLHEI on the outcomes due to method limitations (e.g. using a purposive sampling method, absence of randomization and appropriate control group, lack disaggregation of effect, or low powered analysis and inadequate sample size). Moreover, there is no previously conducted study in Ethiopia.

Therefore, this study aims to improve MHSU among women of reproductive age in Dale and Wonsho districts of the Sidama region, Ethiopia.

The specific objectives are:

**Paper I:** To assess the prevalence and predictors of MHSU among women of reproductive age in Dale and Wonsho districts of the Sidama region, Ethiopia.

**Paper II:** To explore the perceptions, barriers, and facilitators of MHSU among mothers and service providers in Dale and Wonsho districts of the Sidama region, Ethiopia.

**Paper III:** To assess the effect of HEI on the knowledge of mothers regarding ODS and BPCR practice among women of reproductive age in Dale and Wonsho districts of the Sidama region, Ethiopia.

**Paper IV:** To evaluate the effect of HEI on MHSU among women of reproductive age in Dale and Wonsho districts of the Sidama region, Ethiopia.

**Research hypothesis**

• **H_o_:** The CLHEI has no a significant effect on the knowledge of mothers regarding ODS, BPCR practice and MHSU.

• **H_A_:** The CLHEI has a significant effect on the knowledge of mothers regarding ODS, BPCR practice and MHSU.

## Significance of the study

The current study is designed to empower the women with knowledge and skill for improved utilization of existing MHS for the progress of women and newborn health outcomes. These tactics will benefit the governmental organizations, other development allies, and non-governmental organizations to relieve the severe scarcity of human resources in developing countries including Ethiopia. However, the participatory community level and HEI studies for MHC improvement in African regions are scarce. Moreover, there is no previously conducted study in Ethiopia.

Therefore, the epidemiological evidence is a prerequisite to developing appropriate intervention strategies or to filling the existing knowledge gaps. The results from this study will be helpful to inform program managers, policymakers, and implementers in designing effective intervention strategies to improve MHSU and achieve SDGs. The results will also be useful to encourage evidence-based decision-making to address the problems Ethiopian women face throughout the continuum of care. Furthermore, this study will be generated results that can inform the maternal health champions by offering predictors, barriers, and facilitators working in the context of the Sidama region. It also provides evidence for the effective utilization of resources by coming up with an evidence-based recommendation. Moreover, it acts as a source of information for those interested to conduct further studies elsewhere.

**Methods and materials**

**Study area**

This study will be conducted in 2 districts (Dale and Wonsho) of the Sidama region, Ethiopia. Dale district has an overall population of 268, 839 with an estimated total of 53, 768 households (HHs) and comprises an area of 30,212 km2. Of these, 24% were WRA. The district has consisted of two urban and thirty-six rural *kebeles* (the least administrative unit of Ethiopian structures). The Wonsho district has an overall population of 129, 730 with an estimated total of 21, 857 HHs and comprises an area of 14,528 km2. The district has consisted of 1 urban and seventeen rural *kebeles.* Farming or agriculture is the major share of income-producing activity in both districts. The main crops grown in both districts are coffee, *enset* (false banana), khat, barely, khat, haricot beans, corns, sweet potatoes, and local varieties of cabbage. The Dale woreda has consisted of 10 health centers and 33 health posts, whereas Wonsho woreda has 5 health centers and 17 health posts. This site was chosen based on concern of the existing structure to provide a sampling frame, experienced data collectors and supervisors, access to transportation, and a good geographical location.

**Study design**

A community-based cross-sectional study, phenomenological qualitative study, and parallel-group Cluster Randomized Controlled Trial (CRCT) will be used to address the objectives of the current study. The study is a 2 arm CRCT, with every cluster being *kebeles* located in the Dale and Wonsho districts of Sidama region, Ethiopia. The hallmark of this design is each cluster remains in the arm it was randomly assigned to during the course of the whole study period. Thus, all study subjects are randomly assigned into a group and all the study subjects in the assigned group obtain or do not obtain an intervention.

**Study subject**

Study subject will be all WRA, service users and providers, all pregnant women residing in Dale and Wonsho districts of the Sidama region, Ethiopia.

**The inclusion and exclusion criteria**

All systematically selected WRA who gave live birth in the last 12 months, all purposely selected service providers and users, all pregnant mothers residing in the selected *kebeles* for at least for 6 months and have no plan to change residence during the implementation of an intervention, no psychiatric problems, capable of providing written informed consent, and voluntary to be visited by WDT facilitators, data collectors, and supervisors will be included for this study. Women who have a severe illness during the data collection period will be excluded from this study due to unable to communicate. Also, study subject who have a psychiatric disorder will be excluded due to that could affect participation and consent procedure. Similarly, women who experienced stillbirth and infant deaths will be excluded because the questions from this study are expected to re-memorize women the unfavorable pregnancy outcome they had faced. This may seriously affect maternal participation and genuine response. Midwives who have been serving in the maternal and child health case team for less than two years will be excluded. Due to this reason, these midwives have less experience and interaction with pregnant women and couldn’t provide in-depth information on perceptions, barriers, and facilitators of MHSU. Moreover, all WRA included in the quantitative study will be excluded because they have information during the quantitative study that may introduce information bias.

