**Sample size calculation**

The adequate sample size for all objectives is calculated using openepi version 3 software. The sample size needed to estimate the utilization of MHS is calculated assuming the anticipated utilization of ANC (74%), births attended in an HF (48%), and PNC (34%) according to the report of 2019 Mini EDHS[[29](#_ENREF_29)], the margin of error of 5%, 95% confidence interval, 1.31 design effect. Based on the above information, the estimated sample size is 392 (ANC), 508 (births attended in a health facility), and 457 (PNC). The sample size needed for identifying the predictors associated with MHSU is calculated considering variables significantly associated with MHSU based on previous studies done in Northern Ethiopia [7], in rural Haramaya district, Eastern Ethiopia [10], and in Northwest Ethiopia [11]. For all calculations, power was set at 80%, level of confidence at 5%, and the ratio of unexposed-to-exposed were assumed to be 1. Hence, the sample size of 1,104 obtained from the second objective will be utilized due to it is the maximum sample size assessed and would be adequate to assess all objectives of this study. The minimum required sample size for the qualitative study will be determined according to the recommendation of Morse and Creswell for Phenomenological studies (20 in-depth interviews, 9 focus group discussions, and 20 key informant interviews) [[30](#_ENREF_30)]. The minimum required sample size for the third and fourth objectives is calculated based on the following considerations. Due to the lack of the previous cRCT on the same topic, assumptions on the proportion of women with knowledge on ODS in the control and intervention arms were taken from a previous quasi-experimental study. The proportion before the intervention was taken as the proportion in the control arm and the proportion after the intervention as the proportion in the intervention arm. Accordingly, P1 = 45.7% (proportion of women’s knowledge regarding ODS during pregnancy) in the control group, P2= 62.9% (proportion of women’s knowledge regarding ODS during pregnancy in the intervention arm) [[14](#_ENREF_14)], 95% CI, and 80% power. According to the above considerations, the estimated effective sample size for individual-based randomization is 286. For this objective, the sample size is adjusted to non-response rate (NRR) by dividing the initial sample size by the anticipated response rate. In case of knowledge regarding ODS during pregnancy, the adjusted sample size to NRR is 286/1 = 286.The minimum required number of clusters is computed by multiplying the effective sample size and ICC factors for both groups [28]. We received the typical value of ICC factor of 0.01 from range values (0.01 to 0.05) based on the existing recommendation [26]. Consequently, the minimum needed cluster number is 329*0.01 = 3.29 for both groups. Nevertheless, to maintain the sufficiency of the cluster and to have adequate power [26, 28], 12 clusters (*12 kebeles*) will be included in this study. To account for the effect of the cluster, the effective sample size is multiplied by a VIF of 1.26. The VIF is calculated with the assumption of an equal cluster size of 27 study subjects from 12 clusters (*kebeles*). Using ICC value of 0.01, (VIF = 1+ [(n-1) ICC]), where ‘n’ is the average cluster size [28]. Thus, the final estimated sample size is 360 (180 in the intervention arm and 180 in the control arm). However, the sample size calculated for the fourth objective which is designed to evaluate the effect of the intervention on MHSU is 1,126 (i.e., larger). Hence, the sample size of 1,126 obtained from the fourth objective will be utilized for this objective as well as it would be maximum or representatives of the sample for both objectives.

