**The measurements**

**ANC utilization** is measured as a proportion of women who utilized ANC from skilled providers (HEWs, midwives, nurses, health officers, and doctors) at least once during the last pregnancy using a woman's self-report. However, different studies considered different figures of ANC visits being optimum. For instance, some researchers had fixed 2 ANC visits to be adequate. The WHO suggests at least 8 ANC visits throughout pregnancy while the first visit will be conducted before 16 weeks or within the first trimester. Therefore, standardization of the numbers of ANC use is required to assist the comparison of diverse or different studies. Accordingly, we considered utilization of ANC as a woman who has at least one ANC follow-up which is similar to EDHS. Besides, the time must be within the first trimester or before 16 weeks of gestation. Moreover, women must consume more than 90 iron-folic acids (IFA) tablets or syrup, receive at least one dose of tetanus toxoid injection, have a laboratory test result of syphilis, and blood group.

**Institutional delivery utilization** is measured as the proportion of women who utilized institutions (governmental health centers or hospitals, and/or private hospitals or clinics) for delivery in their last pregnancy using a woman’s self-report.

**PNC utilization** is measured as the proportion of women who utilized a PNC visit within 42 days after giving birth at least once using a woman’s self-report.

**Maternal knowledge regarding ODS** will be measured using the 30 questions during three phases namely antepartum (9 questions), intrapartum (12 questions), and postpartum (9 questions). The correct answers are assigned a score of 1, while incorrect answers are assigned a score of 0. Lastly, the total knowledge scores range from 0 to 30. The study respondents who spontaneously mention at least 3 ODS during each phase are classified as having “good knowledge” and those who are not able to spontaneously mention 2 or fewer ODS have “poor knowledge”.

**Spontaneous knowledge** is defined as the knowledge of study participants who can name or call an ODS without being read the name of that sign by data collectors. Merely true ODS spontaneously mentioned by study participants will be recorded during the interview.

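### The Paper I survey sets no minimum time since birth, so women interviewed before day 42 can be miscounted as non-users of postnatal care and its prevalence can only be biased downward

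*Protocol*

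**What the plan says.** The first specific objective (Protocol, Introduction, Paper I) is "To assess the prevalence and predictors of MHSU among women of reproductive age". Maternal health service use has three components, one of which is PNC.

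The inclusion and exclusion criteria cover all study components in one paragraph. The clause that fits the survey is "All systematically selected WRA who gave live birth in the last 12 months". It limits how long ago the birth may have been, but not how recent it may be. None of the listed exclusions concerns time since delivery.

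Under The measurements, PNC use is "the proportion of women who utilized a PNC visit within 42 days after giving birth at least once using a woman’s self-report". The study variables section says that use is captured by yes/no questions.

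The Sample size calculation plans PNC prevalence from "PNC (34%) according to the report of 2019 Mini EDHS", with "the margin of error of 5%, 95% confidence interval, 1.31 design effect", and arrives at 457. The survey uses 1,104, the larger number required for the predictor objective. In the Introduction, the same survey percentage is described differently: "merely 34% of women received postnatal care within 48 hours after childbirth".

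**The concern.** The eligibility window and the outcome window do not fit together. A woman interviewed 10 days after delivery who goes for PNC on day 20 is a user under the 42-day definition. At interview she truthfully answers no, and she enters the numerator as a zero and the denominator as a one. The reverse error cannot arise from this mechanism, so the bias has one direction and does not shrink as the sample grows.

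The Statistical data analysis section does not repair it. Multiple imputation is planned for missing data, but her answer is a recorded no, not a missing value. No rule censors, flags or removes women whose 42 days are still running.

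What is at stake is the PNC prevalence in Paper I and, possibly, the model of its predictors. Antenatal care and institutional delivery are settled by the time of the birth and do not have an open window.

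**Working it through.** **Inputs from the protocol:** birth within 12 months, no lower limit (inclusion criteria); 42-day PNC window (The measurements); P = 34%, margin 5%, design effect 1.31, survey n = 1,104 (Sample size calculation); 34% is a 48-hour figure (Introduction).

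**Assumptions, not in the protocol:** births are spread evenly over the 365 days before interview; the timing of first PNC visits is varied over a range.

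**1. The plan's own figure.** n = 1.31 × 1.96² × 0.34 × 0.66 / 0.05² = 1.31 × 344.8 = 451.7. The protocol states 457, which is 1.2% higher, so the figure is reproduced.

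**2. Women with an open window.** 42/365 = 0.115; 0.115 × 1,104 = 127.

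**3. Bias.** Among women who will use PNC within 42 days, let m be the mean day of the first visit. With evenly spread births, a user is interviewed before her first visit with probability m/365, so

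bias = −P × m/365.

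At P = 0.34:

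- First visits even over the first 48 hours, m = 1: 0.34 × 1/365 = 0.0009, or −0.1 points. Placing every visit at hour 48 (m = 2) gives −0.2.
- First visits uniform over 42 days, m = 21: 0.34 × 21/365 = 0.0196, or −2.0 points (32.0% observed).
- Extreme bound, all on day 42, m = 42: 0.34 × 42/365 = 0.0391, or −3.9 points (30.1% observed).

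**4. Visits after 48 hours.** Because the 34% counts visits within 48 hours only, true 42-day use may be higher. As an illustration, each further 10 points of users with first visits even over days 2 to 42 (mean day 22) adds 0.10 × 22/365 = 0.006, or about 0.6 points of bias. The bias also scales with P: at an assumed 50% it would be 0.50 × 21/365 = 2.9 points under uniform timing and 0.50 × 42/365 = 5.8 at the bound.

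**5. Comparison with sampling error.** 95% half-width at n = 1,104: 1.96 × √(1.31 × 0.34 × 0.66 / 1,104) = 0.032, or 3.2 points.

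**The case against.** The strongest reply is that the effect is negligible on the protocol's own figure. The 34% is care within 48 hours, and visits already made by then cannot be spread over 42 days. On that basis the bias is about 0.1 points, and even 2.0 points is below both the 3.2-point half-width and the 5-point margin accepted in planning. This stands as a limit on size. A reader might infer a 2-point bias from the 34%, but the protocol does not support that: it requires late first visits on which the protocol gives no figure. The reply does not remove the mismatch. Visits after 48 hours are what a 42-day definition adds, and they are the visits most exposed to truncation.

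A reader might also infer that time since birth becomes a false predictor and distorts the others. This is possible but not shown. Time since birth is not among the predictors or covariates listed in The study variables, and no listed one is known to differ by whether the birth fell in the last 42 days. If the open window is unrelated to a predictor, the result is at most slight attenuation of its odds ratio.

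It can be said that the PNC denominator is a matter for an analysis plan. That is fair for a denominator rule alone. But eligibility and the outcome definition are both fixed in the protocol, and followed as written they misclassify some users.

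Two other readings go too far. The survey takes a systematic sample, not every eligible woman, though this leaves the bias unchanged. And 457 is not wrong on this account.

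**Conclusion.** The point holds, with a modest and uncertain size. About 11.5% of the survey sample, some 127 of 1,104 women, would be interviewed before their PNC window closes, given evenly spread births. Those who attend later within 42 days are counted as non-users, so the prevalence estimate can only err downward. At 34% use the bias is about 0.1 points if all first visits come within 48 hours, about 2.0 if they were uniform over 42 days, and at most 3.9, against a half-width of 3.2 points. Which value applies depends on visit timing, which the protocol does not give.

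The point is confined to PNC in an observational component. It does not bear on the randomised comparison or its sample size. It merits action because the correction costs almost nothing, not because a Paper I conclusion has been shown to change.

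**What to change.** In The inclusion and exclusion criteria, state for the Paper I survey that the live birth must have occurred between 42 days and 12 months before the interview. The cost is one screening question on the date of birth. The sample size stays at 1,104 and all of those women have a complete PNC window.

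If eligibility is to stay as it is, restrict the PNC prevalence and the PNC predictor model to women at least 42 days postpartum. This leaves about 1,104 − 127 = 977 women. That exceeds the 457 stated for PNC prevalence, and the half-width only widens to 1.96 × √(1.31 × 0.34 × 0.66 / 977) = 3.4 points. It falls below the 1,104 set for the predictor objective, however, and the protocol does not say which outcome produced that number. Keeping 1,104 evaluable women would take about 1,104 / (1 − 0.115) = 1,248 interviews. The eligibility change avoids this loss and is the better choice.
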